### Intervention

Patients in the three groups will receive GnRH-a or GnRH-A protocol according to the previous study (21, 22). Egg retrieval, fertilization, and embryo transfer were determined by their fertility specialists. During the study period, the patients’ medications, including dose and types, should be recorded in detail.

Following the randomization, the patients who were randomized into the EA + IVF group and the pEA + IVF group will receive EA treatment during the ovarian stimulation phase at three times per week (every other day) until trigger day with a minimum five session. Each session will continue for 30 min. Licensed acupuncturists possessing a minimum of 1 to 3 years of clinical experience will undergo training in a standardized operating procedure. This training aims to impart a comprehensive understanding of the precise locations of acupoints and non-acupoints. Additionally, they will acquire proficiency in needle manipulation and the operation of electro-devices. Only acupuncturists who have completed this training will be authorized to perform acupuncture treatments.

The disposable needles (Hwato, Suzhou, Jiangsu, China) and the SDZ-V EA apparatus (Suzhou Medical Appliance) have the same appearance. The needle device used for blinding is comprised of a sticky plastic plate with a guide tube. The needles and blunt-tip needles will be administered through the guide tube and the hole of the plastic plate.

#### Electro-acupuncture

The treatment protocol, guided by the TCM theory, is aimed to enhance ovarian response and endometrium receptivity and served as an adjunctive non-pharmacological therapy. The treatment will involve the alternation between two sets of acupuncture points. Set 1 will administer in the supine position, including GV20 (*Baihui*), CV12 (*Zhongwan*), ST25 (*Tianshu*), CV 6 (*Qihai*), CV4 (*Guanyuan*), GB26 (*Daimai*), KI12 (*Dahe*), EX-CA1 (*Zigong*), SP10 (*Xuehai*), ST36 (*Zusanli*), SP6 (*Sanyinjiao*), and LR3 (*Taichong*). Set 2 will administer in the prone position, including BL23 (*Shenshu*), BL32 (*Ciliao*), and KI3 (*Taixi*) (see details in **Table 2**, **Figure 2**). All of the acupoints will be located according to the “WHO Standard Acupuncture Point Locations in the Western Pacific Region” (23). Following needle insertion, small, equal manipulations of twirling, lifting, and thrusting will be performed on all needles to reach *De qi* (a composite of sensations including soreness, numbness, distention, heaviness, and other sensations) (18). Paired alligator clips from the EA apparatus will be attached transversely to the needle holders at bilateral ST25 and EX-CA1 and at bilateral ST36 and SP10 in the supine position, while needles at bilateral BL23 and BL32 were in the prone position. The EA stimulation will be with a dilatational wave of 2/100 Hz and a current intensity of 0.1 to 5 mA depending on the participant’s comfort level (preferably with skin around the acupoints shivering mildly without pain).

**Table 2 T2:** Location of acupoints and manipulation techniques used for the EA+IVF group.

Acupoints	Location	Manipulation
Set 1 acupoints		
GV 20 (*Baihui*)	5 cun directly above the midpoint of the front hairline	Transverse insertion to a depth of 0.5 cun^a^–0.8 cun
CV12 (*Zhongwan)*	4 cun to the navel, on the upper abdomen middle	Inserted vertically to a depth of 1.0 cun–1.5 cun
ST25 (*Tianshu)*	Bilateral, 2 cun lateral to the umbilicus	Inserted vertically to a depth of 1.0 cun–1.5 cun
GB26 (D*aimai)*	Bilateral, 1.8 cun below to *Zhangmen* (*Zhangmen*, below the free end of the 11th floating rib)	Inserted vertically to a depth of 1.0 cun–1.5 cun
CV 6 (*Qihai*)	1.5 cun below the umbilicus, on the anterior midline	Inserted vertically to a depth of 1.0 cun–2.0 cun
CV4 (*Guanyuan*)	3 cun below the umbilicus, on the anterior midline	Inserted vertically to a depth of 1.0 cun–2.0 cun
KI12 (*Dahe)*	Bilateral, 4 cun below the umbilicus, and 0.5 cun lateral to the lower anterior midline	Inserted vertically to a depth of 0.5 cun–1.0 cun
EX-CA1 (*Zigong)*	Bilateral, 3 cun lateral to the umbilicus, and 4 cun lateral to the lower anterior midline	Oblique insertion to the uterus location direction to a depth of 0.8 cun–1.2 cun
SP10 (*Xuehai*)	Bilateral, 2 cun above the upper border of the patella	Inserted vertically to a depth of 1.0 cun–1.5 cun
ST36 (*Zusanli*)	Bilateral, 3 cun directly below *Dubi*, and one finger-breadth lateral to the anterior border of the tibia (*Dubi*, in the lateral depression of the patellar ligament, when the knee is flexed)	Inserted vertically to a depth of 1.0 cun– 2.0 cun
SP6 (*Sanyinjiao*)	Bilateral, 3 cun above the tip of the medial malleolus	Inserted vertically to a depth of 1.0 cun–1.5 cun
LR3 (*Taichong*)	Bilateral, in the depression anterior to the junction of the first and second metatarsal bones	Inserted vertically to a depth of 0.5 cun– 0.8 cun
Set 2 acupoints		
BL23 (*Shenshu*)	Bilateral, 1.5 cun lateral to the depression below the spinous process of the second lumbar vertebra	Inserted vertically to a depth of 0.5 cun–1.0 cun
BL 32 (*Ciliao*)	Bilateral, in the sacral region, below the anterior superior iliac spine, and precisely at the site of the second sacral foramen	Inserted vertically to a depth of 1.0 cun–1.5 cun
KI 3 (*Taixi*)	Bilateral, on the medial side of the foot, at the depression between the tip of the medial malleolus and the Achilles tendon	Inserted vertically to a depth of 0.5 cun–1.0 cun

a 1 cun (approximately 20 mm) is defined as the width of the interphalangeal joint of the patient’s thumb.

EA, electro-acupuncture; COH, controlled ovarian hyperstimulation.

**Figure 2 f2:**
[figure not shown]
Locations of acupoints and non-acupoints. NA, non-acupoint.

#### Placebo electro-acupuncture

The participants in the pEA group will receive acupuncture with a pragmatic placebo needle on non-acupoints with no skin penetration. *Deqi* and manual stimulation in the group should be avoided. Non-acupoints (NA) deviate from the conventional acupoints or meridians. The locations of the non-acupoints are shown in **Table 3** and **Figure 2**. The same electrical stimulation device with a wave of 2/100 Hz and a current intensity of 0.1 mA will be applied. The paired electrodes will be connected to theneedles at bilateral NA-3 with NA-7 and at NA-9 with NA-10 in the supine position, while needles at bilateral NA-13 and NA-14 in the prone position will minimize electricity superficially.

**Table 3 T3:** Location of points and manipulation techniques used for pEA+IVF study groups.

Acupoints	Location	Manipulation
Set 1 acupoints		
Non-acupoint 1	3.5 cun directly above the midpoint of the front hairline, 1 cun^a^ to GV21 (*Qianding*) (applied on body side alternatively on each treatment session)	Non-penetrating
Non-acupoint 2	4 cun above the umbilicus, 1 cun lateral to CV 12 (*Zhongwan*) (applied on body side alternatively on each treatment session)	Non-penetrating
Non-acupoint 3	Bilateral, 1 cun lateral to ST 25 (*Tianshu*), the midpoint between ST25 and SP15 (*Daheng*)	Non-penetrating
Non-acupoint 4	1.5 cun below the umbilicus, 1 cun lateral to CV6 (*Qihai*) (applied on body side alternatively on each treatment session)	Non-penetrating
Non-acupoint 5	3 cun below the umbilicus, 1 cun lateral to CV4 (*Guanyuan*) (applied on body side alternatively on each treatment session)	Non-penetrating
Non-acupoint 6	Bilateral, 0.5 cun lateral to KI 12 (*Dahe*), the midpoint between KI 12 and ST 29 (*Guilai*)	Non-penetrating
Non-acupoint 7	Bilateral, 0.5 cun lateral to EX-CA1 (*Zigong*), the midpoint between EX-CA1 and SP13 (*Fushe*)	Non-penetrating
Non-acupoint 8	Bilateral, 1 cun below to GB26 (D*aimai*)	Non-penetrating
Non-acupoint 9	Bilateral, 0.8 cun medial to the midpoint of the line linking the anterior superior iliac spine and the lateral end of the base of patella	Non-penetrating
Non-acupoint 10	Bilateral, 1 cun lateral to ST36 (*Zusanli*), between stomach meridian of foot Yangming and gallbladder meridian of foot Shaoyang	Non-penetrating
Non-acupoint 11	Bilateral, 3 cun above the tip of the medial malleolus between SP 6 (*Sanyinjiao*) and Achilles tendon	Non-penetrating
Non-acupoint 12	Bilateral, in the depression anterior to the junction of the third and fourth metatarsal bones	Non-penetrating
Set 2 acupoints		
Non-acupoint 13	Bilateral, 1 cun lateral to BL23 (*Shenshu*)	Non-penetrating
Non-acupoint 14	Bilateral, 1 cun lateral to BL32 (*Ciliao*)	Non-penetrating
Non-acupoint 15	Bilateral, 2 cun above KI 3(*Taixi*).	Non-penetrating

a 1 cun (approximately 20 mm) is defined as the width of the interphalangeal joint of the patient’s thumb.

EA, electro-acupuncture; COH, controlled ovarian hyperstimulation.

Throughout the intervention, the acupuncturists will maintain minimal verbal communication with the participants. Patients will be treated separately to prevent communication, and they were asked to document any other treatments that they had.

#### IVF control group

Patients in the IVF control group will not receive any EA treatment during the ovarian stimulation phase. After the end of the follow-up period, the participants will receive compensation after the follow-up period ends.

### Outcome measurement

The assessors will record the baseline characteristics, including the couple’s age, ethnicity, body mass index (BMI), diagnosis of infertility, infertility history, previous IVF cycles, the level of AMH, AFC, the level of FSH, and LH. Ovarian response parameters (duration of stimulation, total dose of gonadotrophins, peak E2 level, and number of oocytes retrieved) will be used to assess the ovarian function during the ovarian stimulation (**Table 4**). The duration of stimulation is calculated from the first day of administrating gonadotropin to the hCG trigger. After the treatment, the participants will be questioned about the group allocation that they received.

**Table 4 T4:** Diagnosis definitions and time frame of outcomes.

Diagnosis	Definition	Time frame
Primary outcomes		
Clinical pregnancy^a^	Ultrasound-confirmed gestational sac	28 days after embryo transfer
Secondary outcomes		
Recruitment process		
Patient retention rate	The percentage of patients enrolled at baseline, who completed all follow-up measurements	Study completed
Adherence to treatment	Attendance at the treatment sessions	Study completed
Data on ovary induction		
Total dose of gonadotrophins (IU)	Was measured as the total dosage of gonadotropin drugs during the ovarian stimulation phase	On trigger day
Endometrium thickness (cm)	Was measured in the midsagittal plane of the thickness of the bilateral endometrium	On trigger day
Estrogen level pg/mL	Level of estrogen in the peripheral blood	On trigger day
Embryo data		
Ovum retrieved	Number of eggs retrieved from bilateral ovaries	On trigger day
High-quality embryos	Number of high quality measured by embryologists	3 or 5 days after the ovum was retrieved
Pregnancy outcomes		
Biochemical pregnancy^a^	Serum human chorionic gonadotropin ≥10 mIU/mL	10–14 days after embryo transfer
Early miscarriage^a^	Fetal growth stops or the absence of heart activity in the gestational sac within the first 12 weeks of pregnancy	Before 12 weeks in gestational age
Score of the questionnaires		
SAS	SAS consists of 20 items, and its measurement is determined by calculating the sum of the scores of each item	Baseline and on trigger day
SDS	SDS consists of 20 items, and its measurement is determined by calculating the sum of the scores of each item	Baseline and on trigger day
FertiQoL	FertiQoL contains 36 items, and its measurement is determined by calculating the sum of the scores of each item	Baseline and on trigger day
PSQI	PSQI contains 19 items, and its measurement is determined by calculating the sum of the scores of each item	Baseline and on trigger day
Adverse events		
	Including nausea during the ovarian stimulation, hematoma around the site of needling, infection around the site of needling, dizziness after acupuncture, and other discomforts after acupuncture	After each treatment

a The rates of pregnancy outcomes are defined as the number of pregnancy outcome cycle per ovarian stimulation cycle.

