#### Inclusion criteria

Women who are diagnosed with infertility (1) and will undergo IVF or Intracytoplasmic sperm injection (ICSI) who have met the following criteria will be recruited: (1) ages between 21 to 42 years old, (2) with GnRH-a or GnRH-A ovarian stimulation protocol, (3) AMH >1.2 ng/mL (20), (4) previous IVF/ICSI cycle ≤2, and (5) written informed consent.

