### Randomization and allocation concealment

Randomization will be conducted after the patients agree to consent to undertaking acupuncture treatments. Patients will be randomized according to the randomized number table generated by SPSS (version 27.0, IBM, Armonk, NY, USA) after completing the baseline assessments. Patients will be randomized into three groups: electro-acupuncture with IVF treatment (EA+ IVF group), placebo electro-acupuncture with IVF treatment (pEA + IVF group), and only IVF control (IVF group) in a 1:1:1 ratio using stratified block randomization (block = 3 or 6, randomly). An independent statistician with no clinical role in this study will comply with the randomization sequence. Allocation concealment was ensured by using a telephone by an independent third party to ensure objectivity and minimize the risk of bias.

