#### Scale and questionnaire measurement

Anxiety and depression are the most prevalent mental illnesses contributing to the global infertility burden, which are also potential risk factors for IVF success. Emotional disorder can also lead to sleep problems and will influence the quality of life. Therefore, the scale and questionnaire measurement will be measured at baseline and on the trigger day to learn about changes in the mental disorder after the acupuncture treatments (**Table 4**). Self-rating anxiety scale (SAS) (29) and the self-rating depression scale (SDS) (30) are 20-item Likert scales, with raw scores that range from 20 to 80, which are converted to index scores by dividing the sum of the raw scores by 80 and multiplying by 100. Higher scores indicate greater severity of anxiety or depression symptomology. Index scores, 25–49 (raw scores 20–40); normal, 50–59 (raw scores 41–47); mild to moderate, 60–69 (raw scores 48–55); moderate to severe; and 70 and over (raw scores 56 and over), severe (31). The Pittsburgh Sleep Quality Index (PSQI) is a self-rated questionnaire to assess sleep quality and disturbance that can be used in clinical practice and research studies for patients with psychiatric or sleep problems and even among the general population (32). It contains 19 items in seven subdomains, including subjective sleep quality, sleep latency, sleep duration, habitual sleep efficiency sleep disturbances, use of sleeping medication, and daytime dysfunction (32). The sum scores of each item range daytime dysfunction from 0 to 21. The higher the patients’ scores, the worse sleep quality they experience. The fertile quality of life (FertiQoL) is an instrument to measure the quality of life in men and women experiencing fertility problems (33). FertiQoL consists of 36 items that assess core (24 items) treatment-related quality of life (QoL) (10 items) and overall life and physical health (two items). The items in the prototype FertiQoL survey were randomly presented and rated on a scale of 0–4, where higher scores indicated a more favorable quality of life.

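### The 36-item FertiQoL sum includes 10 treatment items that may not apply at baseline, so the baseline total and the change from it are hard to interpret

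*Protocol article*

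**What the plan says.** Table 4 (Outcome measurement) lists FertiQoL as a secondary outcome at baseline and on trigger day, with one score: "FertiQoL contains 36 items, and its measurement is determined by calculating the sum of the scores of each item".

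The section Scale and questionnaire measurement breaks the instrument into "core (24 items) treatment-related quality of life (QoL) (10 items) and overall life and physical health (two items"), with items "rated on a scale of 0–4, where higher scores indicated a more favorable quality of life". It gives the purpose of measuring twice: "the scale and questionnaire measurement will be measured at baseline and on the trigger day to learn about changes in the mental disorder".

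On timing, patients are randomized "after completing the baseline assessments" (Randomization and allocation concealment), and Table 1 puts the baseline FertiQoL in the screening column, ahead of ovarian stimulation. Table 1 marks the second FertiQoL under oocyte retrieval, whereas Table 4 says trigger day. That is a separate inconsistency and does not affect this point, since both fall after stimulation has begun.

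On treatment history, the Inclusion criteria require "previous IVF/ICSI cycle ≤2", so women with no earlier cycle can enter. Previous cycles are recorded at baseline, but no expected distribution is given.

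On analysis, the Statistical analysis section compares the questionnaire scores among groups at baseline and after treatment. It names no change-score or baseline-adjusted model. Missing outcome data go to multiple imputation, and items that do not apply are not mentioned.

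**The concern.** A sum measures the same thing on two occasions only if the same items can be answered, with the same referent, both times. Ten of the 36 items ask about treatment. A woman who has had no fertility treatment before baseline may have nothing to rate on them. A woman with earlier cycles may rate a past cycle at baseline and the current one on trigger day. The total, and each woman's change in it, then depends partly on treatment history rather than on quality of life.

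A plain sum makes this worse. A blank item either counts as zero, which reads as the worst possible quality of life, or makes the total missing and sends it to imputation. Multiple imputation is meant for values that exist but were not observed. Filling in items that do not apply would invent ratings of treatment not yet received.

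At stake are the baseline description of the sample, the within-arm change that the article says it wants to learn about, and the precision of any between-arm comparison of change. Because the pilot is meant to support a later definitive trial, the scoring could also be carried forward.

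**Working it through.** **Inputs from the protocol article**
- Items: 24 core, 10 treatment-related, 2 overall; each scored 0–4, higher is better (Scale and questionnaire measurement).
- Score: one sum of 36 items at both visits (Table 4).
- Arm size: 38 randomized, 30 after the assumed 20% dropout (Sample size).

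**Assumptions, because the article gives no figure**
- Share f of women whose ten treatment items are blank at baseline: 0 to 100%.
- Mean item score m: 1, 2 or 3, the same at both visits, so that true quality of life is unchanged.
- Blanks count as zero. This is the unfavourable case; the article does not state it.

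**Step 1. Item count.** 24 + 10 + 2 = 36, which reproduces Table 4.

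**Step 2. Weight of the treatment items.** The full sum runs from 0 to 36 × 4 = 144. The treatment items carry 10 × 4 = 40, and 40/144 = 27.8%. The 24 core items run from 0 to 24 × 4 = 96.

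**Step 3. One affected woman with no true change.** Baseline total = 26m, trigger-day total = 36m, artificial rise = 10m.

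| m | Baseline | Trigger day | Rise |
|---|---|---|---|
| 1 | 26 | 36 | 10 |
| 2 | 52 | 72 | 20 |
| 3 | 78 | 108 | 30 |

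The ceiling is 40, at m = 4. The rise is 0 for a woman who answers the ten items at the same level both times.

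**Step 4. Average over an arm.** Mean artificial rise = f × 10m. At m = 2:

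| f | 0% | 25% | 50% | 75% | 100% |
|---|---|---|---|---|---|
| Rise | 0 | 5 | 10 | 15 | 20 |

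**Step 5. Between arms.** Randomization makes f equal across arms in expectation, so the expected between-arm difference in the artefact is 0. Chance imbalance in f between two arms of n has SD √(2f(1−f)/n). For f from 25% to 75% and n of 30 to 38 this is 0.099 (f = 25% or 75%, n = 38) to 0.129 (f = 50%, n = 30). Multiplied by the 20-point shift at m = 2, it adds noise of about 2.0 to 2.6 points (SD) to a between-arm difference in change.

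**Step 6. Trigger day alone.** By then women in all three arms are in treatment, and the trigger-day total does not use the baseline value. A comparison of arms on that day is unaffected.

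**The case against.** The strongest objection is that the article never says that any woman cannot answer the treatment items. It gives no item wording, recall period or rule on who should respond. Women with no earlier IVF are not necessarily untreated: they are diagnosed patients of a reproductive center, and infertility history is recorded separately from previous cycles. This stands. A reader might infer that every first-cycle woman is unable to rate the ten items, but the documents do not support that. The accurate condition is no fertility treatment before baseline, and the accurate verb is may.

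Second, the sum wording in Table 4 is repeated for all four questionnaires and is not a complete scoring rule. SAS and SDS are converted to index scores in the text, and PSQI is described there with seven subdomains and a 0–21 total. This is fair, but for FertiQoL the text names the parts without giving any score other than the 36-item sum. The point therefore concerns a stated rule, not a detail left to a fuller document.

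Third, a reader might infer a bias between arms, or a general false rise of a definite number of points. Neither is supported. Randomization balances the artefact in expectation. A definite figure would need every affected woman to leave all ten items blank, blanks to count as zero although missing outcomes are to be imputed, and a known share of affected women. The range has to start at 0.

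Fourth, change from baseline is a stated purpose but not a named analysis, the outcome is secondary, and the pilot's results are declared exploratory. All of this stands and sets the priority.

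**Conclusion.** The point holds in a limited form. Summing all 36 items at a visit before stimulation, in a sample that may include women without fertility treatment, makes the baseline total and the within-person change depend on treatment history as well as on quality of life.

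The size cannot be fixed from the article. It runs from 0 up to about 20–30 points of 144 for a woman whose ten items count as zero at baseline and average 2–3 on trigger day. It depends on the share of such women and on the handling of blanks.

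The baseline total, the within-arm change and the precision of a between-arm comparison of change are affected. The trigger-day comparison between arms, the primary outcome and the feasibility targets are not. Low priority.

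**What to change.** In Table 4, define the FertiQoL outcome as the 24-item core score (0–96) at baseline and on trigger day. Report the ten treatment items as a separate score, compared between arms on trigger day. Report the two overall items separately. Do not sum all 36.

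This should be done at scoring, from the items already collected. The first patient was randomized in August 2023, and removing items from the baseline form during recruitment would give early and late participants different forms and discard answers from women who have had treatment.

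The cost is a change of wording in Table 4 and more than one reported score. No visit, patient or data item is added.

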#### Primary outcome

In this feasibility and prior study, the primary outcome is the CPR, defined as the rate of achieving clinical pregnancy from the first fresh/frozen embryo transfer cycle with an ultrasound-confirmed gestational sac in the uterine cavity (24) as measured 28 days after embryo transfer.

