## Abstract

**Introduction:**

*In vitro* fertilization (IVF) is a technology that assists couples experiencing infertility to conceive children. However, unsuccessful attempts can lead to significant physical and financial strain. Some individuals opt for electro-acupuncture (EA) during IVF, even though there is limited evidence regarding the efficacy of this practice. Thus, this pilot study aims to explore the effectiveness and safety of EA during IVF on pregnancy outcomes.

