Therefore, we have proposed to conduct a prospective, parallel, randomized, placebo-controlled trial that will be carried out to investigate the efficacy and safety of acupuncture treatment for patients with infertility, comparing them with placebo electro-acupuncture and IVF control groups. The current pilot study aims to assess the feasibility of performing a large-scale RCT, including patient recruitment, retention, and treatment adherence.

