### Sample size

The purpose of this study was to evaluate the study’s feasibility and support the development of a future definitive RCT. Utilizing the upper confidence limit method, we determined that a pilot sample size of between 20 to 40 individuals can serve as a benchmark (34). Based on the consensus of the methodologists, statisticians, and acupuncturists, we decided that a sample size of 30 in each group (25) and a 20% estimated dropout rate were sufficient; thus, the total of 114 patients would be considerable (38 in each group).

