### Statistical analysis

Intention-to-treat (ITT) analysis encompassing all randomized patients will be conducted for all efficacy analyses. Additionally, a per-protocol (PP) analysis focusing on the primary outcome will be performed as a sensitive analysis, excluding patients who did not complete the acupuncture treatment. Missing outcome data will be complemented using multiple imputations with the package “Mice” from the R software (www.r-project.org).

Categorical variables will be reported by number and percentage, whereas continuous variables will be represented by mean and standard deviation (SD) (or median and interquartile range, IQR). The retention rate and treatment adherence will be reported in descriptive statistics.

For the primary outcome, CPR will be compared by the proportions of included patients with clinical pregnancy. To determine the independent factors, logistic regression will be used to identify baseline variables that are associated with outcomes. The retention rate and rates of biochemical pregnancy, ongoing pregnancy, blinding assessments, and adverse events will undergo statistical analysis using chi-squared tests or Fisher’s exact test. Other outcomes will be evaluated using one-way variance (ANOVA) models or Kruskal–Wallis analysis. The score of SAS, SDS, FertiQol, and PSQI, respectively, will be assessed at baseline and after treatment among groups on hCG trigger day. Statistical significance will be determined at *P <*0.05. Pairwise comparisons will be performed between the EA + IVF group and the pEA + IVF group and between the EA + IVF group and the IVF group in a *post hoc* analysis.

A predetermined subgroup analysis will be performed to determine whether the baseline characteristics (female age, ovarian stimulation protocol, etc.) affect the CPR to EA. The data was analyzed using SPSS version 27.0 (IBM, Armonk, NY, USA). As this is a pilot study, our results were considered exploratory.

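### Aim, sample size and primary outcome do not line up: the trial is sized as a feasibility pilot, but clinical pregnancy is its sole primary outcome and is compared at P<0.05

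*Protocol article*

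**What the plan says.** The protocol article states its purpose in more than one way.

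- Introduction, last paragraph: "The current pilot study aims to assess the feasibility of performing a large-scale RCT, including patient recruitment, retention, and treatment adherence". The sentence before it, however, says the trial is to investigate efficacy and safety.
- Sample size: "The purpose of this study was to evaluate the study’s feasibility and support the development of a future definitive RCT". The number is 30 per group, taken from a pilot benchmark of 20 to 40 and agreed by consensus, then raised for 20% dropout to 38 per group and 114 in total. No expected CPR, difference or power enters it.
- Abstract: "this pilot study aims to explore the effectiveness and safety of EA during IVF on pregnancy outcomes".

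On outcomes and analysis:

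- Primary outcome: "In this feasibility and prior study, the primary outcome is the CPR". Table 4 likewise lists clinical pregnancy as the only primary outcome.
- Statistical analysis: "For the primary outcome, CPR will be compared by the proportions of included patients with clinical pregnancy", and "Statistical significance will be determined at *P <*0.05". Pairwise comparisons of EA with placebo EA and of EA with IVF alone follow as post hoc analyses. There is also a per-protocol analysis of the primary outcome and a subgroup analysis of CPR. The section ends: "As this is a pilot study, our results were considered exploratory".
- Secondary outcomes: this section holds the targets that define a successful pilot, namely 114 recruited in 4 months, 80% retention, and at least four sessions attended. Table 4 lists retention and adherence as secondary and has no row for recruitment.

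**The concern.** A primary outcome should answer the question the trial was set up and sized to answer. Here the purpose in the Introduction and the basis of the sample size both point to feasibility, while the primary label and the significance threshold point to efficacy. The measures that answer the feasibility question sit among the secondary outcomes.

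The practical risk lies in the report. With CPR as the sole primary outcome and a P<0.05 rule in the plan, the natural lead result is a significance verdict on CPR from a sample that was never sized for one. A non-significant result would be likely even if EA had a large effect. A significant one would tend to overestimate the effect. Neither would say whether the definitive trial can recruit, retain and treat its participants.

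**Working it through.** **Inputs from the protocol.** 30 per group before dropout, 20% dropout, 38 per group and 114 in total (Sample size); significance at P<0.05 (Statistical analysis), taken as two-sided; 80% retention target (Secondary outcomes).

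**Assumption.** The protocol gives no expected CPR, so control rates of 30%, 40% and 50% are used to show a range.

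**1. The plan's own figure.** 30 / (1 − 0.20) = 37.5, rounded up to 38; 3 × 38 = 114. This reproduces. The starting 30 is a benchmark, so there is no power calculation to reproduce. (The 118 in the Abstract and Discussion is a separate discrepancy and does not affect what follows.)

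**2. Precision of a CPR difference.** Half-width of the 95% CI with both arms at rate p: 1.96 × √(2p(1 − p)/n).

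| Control CPR | n = 38 per arm | n = 30 per arm |
|---|---|---|
| 30% | 20.6 points | 23.2 points |
| 40% | 22.0 points | 24.8 points |
| 50% | 22.5 points | 25.3 points |

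Example: 1.96 × √(2 × 0.3 × 0.7/38) = 0.206.

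**3. Power for one pairwise comparison.** Power = Φ[(d − 1.96 × √(2p̄(1 − p̄)/n)) / √((p₁(1 − p₁) + p₂(1 − p₂))/n)], where d = p₂ − p₁ and p̄ is the mean of the two rates. Example with n = 38, 30% against 50%: (0.20 − 1.96 × 0.1124)/0.1100 = −0.18, which gives power of 0.427.

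Across control rates of 30% to 50%:

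| | n = 38 per arm | n = 30 per arm |
|---|---|---|
| Power, 10-point gain | 14% to 15% | 12% |
| Power, 20-point gain | 41% to 43% | 34% to 35% |
| Gain detectable with 80% power | 30.2 to 31.6 points | 33.5 to 35.5 points |

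For 80% power, a 20-point gain would need 93 to 97 per arm, and a 10-point gain 356 to 388 per arm. A three-arm chi-squared test with only EA better by 20 points has power of 34% to 45% over the same range, so the overall test does not change the picture.

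**4. Precision of retention.** 80% of 114 is 91.2. Retention of 91/114 is 79.8%, with a Wilson 95% CI of 71.5% to 86.2%. The sample estimates retention far more closely than a CPR difference. Even so, a result near the target has an interval on both sides of 80%.

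**5. The attendance target.** It gives a number of sessions but no proportion of participants who must reach it. It cannot apply to the IVF control arm, which receives no acupuncture. Its four sessions also differ from the five-session minimum in the Abstract and the Intervention section.

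**The case against.** The strongest reply is that the plan already guards against this problem. The Secondary outcomes section defines pilot success by recruitment, retention and attendance, and CPR is not among the targets. The Statistical analysis section calls the results exploratory and the pairwise comparisons post hoc. The Discussion plans a larger multicentre study. The aim is also mixed, since the Abstract and the Introduction both mention efficacy or effectiveness, so an exploratory clinical primary outcome is a defensible choice. Low power is normal in a pilot that claims none.

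Much of this stands. A reader might infer that the decision to run the definitive trial depends on CPR or its P value. No section says so, and the success targets point the other way. A reader might also infer that the sample settles the feasibility question because retention is estimated more tightly than CPR. The interval of about 72% to 86% does not support that when retention is close to 80%. How readers would interpret a non-significant CPR is conjecture.

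The reply does not remove the mismatch. The exploratory sentence leaves CPR as the sole primary outcome and leaves the P<0.05 rule in the same section. The dual aim is itself part of the misalignment, because the sample size serves only one half of it. Replacing a primary outcome while recruitment is under way, with unblinded acupuncturists, also invites criticism for outcome switching, so the remedy should not depend on that step.

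**Conclusion.** The concern holds as a mismatch between stated aim, sample size and primary outcome. It does not hold as a claim that progression to the definitive trial hangs on CPR.

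The significance test on the primary outcome is poorly matched to this sample. With 30 to 38 per arm, the 95% CI for a CPR difference is about ±21 to ±25 points, and 80% power requires a gain of about 30 points or more. These figures assume a control CPR of 30% to 50%, which the protocol does not state, and a two-sided 5% test with no adjustment for two comparisons. The existing pilot targets and the exploratory caveat limit the harm. The point is worth acting on because better reporting rules cost little.

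**What to change.** 1. State that the conclusion on proceeding to the definitive trial rests on the pilot targets in the Secondary outcomes section. Report those that are proportions with 95% CIs, and accept in advance that retention near 80% will not be shown to lie above or below the target. Adding recruitment to Table 4 would make the set complete.
2. Before using the attendance target as a criterion, express it as a proportion of participants in the two acupuncture arms. Reconcile the four sessions there with the five-session minimum in the Abstract and the Intervention section.
3. Report CPR as arm proportions and as differences with 95% CIs for EA against placebo EA and EA against IVF alone. State that no efficacy conclusion will be drawn from P<0.05.
4. Align the aim in the Abstract with the feasibility purpose in the Introduction and Sample size sections.

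The cost is protocol wording; no visit, data item or participant number changes. Relabelling CPR from primary to exploratory is optional. If it is done, the change must be dated and disclosed as made during recruitment and before unblinding, with the registry updated. Otherwise, keep CPR openly as the prespecified primary outcome and apply the four changes above.
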